Most studies on single-implant overdentures have used stud attachments, such as O-balls or cylindrical patrices [13–16, 21]. These systems tend to considerably improve the performance of mandibular dentures, but require regular maintenance, including change or activation of matrices. Although the incidence of matrix maintenance for single implant overdentures is comparable to that of two-implant alternatives, more than half of patients may need some reactivation, tightening, or reattachment of retentive components over a single year [13]. Such maintenance needs vary considerably among attachment systems and can be minimized by using large O-balls, e.g. 5.9-mm-wide patrices [21]. Nevertheless, this may be clinically inconvenient due to the reduced bulk of denture bases following attachment insertion and, therefore, higher risk of fracture [13].

Alternatives to well-known attachment systems may result in lower maintenance needs and other favorable characteristics. One of those alternatives is a new type of attachment dubbed Novaloc, based on mechanical retention from a polyetheretherketone (PEEK) matrix on a cylindrical patrix, that may be more resistant to wear than the nylon used in other systems. The abutments also receive an amorphous diamond-like carbon surface coating that minimizes roughness and is intended to enhance resistance of the attachment components.

In spite of the potential advantages of the Novaloc system for single implant overdentures, no previous trial has evaluated this system’s performance. A search in PubMed for the terms [overdenture* AND (PEEK OR polyetheretherketone OR “Polyether ether ketone” OR “poly-ether-ether-ketone”)] revealed a single report on bar-clip systems (1 December 2017). This suggests that there are no published clinical studies on Novaloc or any other stud system based on PEEK matrices or carbon-coated patrices. An in vitro study, however, shows promising results regarding the long-term retention of PEEK matrices compared to the traditional Locator system [22].

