### Study outcomes

All patient-reported outcomes, except for prosthesis rotation, will be collected at baseline, together with sociodemographic data, including age, gender, level of education, and income. Clinical data will be also collected before treatment, such as ridge morphology [28], amount of time edentulous, and age of existing dentures.

Participants will return for outcome assessment after three months using each attachment, for a total follow-up time of six months. A three-month period is enough to observe a significant decrease in the retention force of Locators [29] but is of unlikely length for adverse events associated with other components. Moreover, a slightly longer period, i.e. six months, results in similar patient satisfaction with mandibular overdentures [30]. Participants will be evaluated again 12 months following the cross-over trial for an appraisal of maintenance needs/adverse events. A 12-month period will be enough to reveal attachment maintenance events for most participants with Locators [21], as well as some uncommon events, e.g. denture base fractures [13].

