In each assessment session, participants will provide data on:Satisfaction with overdentures. The McGill VAS Satisfaction questionnaire [31] will be used to measure general satisfaction (primary outcome), as well as satisfaction with other functional aspects of the prostheses using 100 mm VAS. Other aspects include ability to chew, comfort, stability, aesthetics, ability to speak, and ability to clean. Some of the 13 items in the questionnaire include ability to chew specific foods (lettuce, soft bread, hard cheese, steak, raw apple, and raw carrot). These were selected because they represented different textures and hardnesses and were ranked by a group of complete denture patients from “very easy” to “very difficult” to chew. Patients will rate their ability to chew these foods on a 100 mm VAS with anchors of “not at all difficult to chew” to “impossible to chew.” Patients will be trained to use this type of scale before answering the questionnaires. Previous studies have shown good properties for the McGill VAS Satisfaction questionnaire. Besides good internal consistency and reproducibility [32], its ability to discriminate between different clinical conditions denotes good construct validity [30, 33].Oral health-related quality of life. Participants will be asked to complete the Oral Health Impact Profile for edentulous people (OHIP-EDENT), which is an abbreviated version of the original 49-item OHIP that was tested specifically with edentulous populations [34]. This questionnaire is composed of 20 items that can be grouped into subscales, representing different domains/dimensions of perceived impact, such as functional limitation or social disability. This abbreviated version shows good reliability and discriminant validity, similar to the original OHIP [34]. Although seven subscales were originally purported [35], we will use a four-domain model as recommended by recent factor analysis studies [36, 37].Overdenture rotation. Patient perception of rotation of the mandibular overdenture will be assessed by two questions, as used by Kimoto et al. [38]: (1) Does your denture lift at the back when you chew? (yes-no); (2) How much does the lifting of your denture bother you? (100 mm VAS).Clinician-based outcomes will be assessed for each three-month period. Participants will be evaluated based on a standardized clinical form, which will be completed immediately following each appointment. Overdentures will be classified as successful if they can function in the way that they were intended, with additional retention provided by the attachment system. For the determination of implant success and survival, the implants will be classified at each data collection appointment according to Misch et al. [39]. Clinical evaluation will also include the following parameters [30]: (a) presence of plaque; (b) presence of calculus; (c) depth of peri-implant pockets; (d) bleeding on probing; (e) signs of swelling or inflammation. The presence of suppuration and tenderness will also be noted. Probing depth will be measured at four sites for each implant (mesially, labially, distally, and lingually) using a periodontal probe.Treatment costs. We intend to gather data on both direct and indirect costs to compare the differences in cost-effectiveness between the two attachments systems. The effectiveness is measured by any difference in overall patient satisfaction (primary outcome) at baseline and at the three- and six-month follow-up visits. The size of the effect may vary at each of the two intervals. This analysis is based on the following assumptions: (1) the total cost at the end of the 6-month evaluation period would be the same between sequences 1 and 2; (2) the implant placements are deemed clinically successful at given intervals (three and six months post treatment); (3) no surgical or prosthetic complications are encountered during the six-month post-treatment period. Cost-effectiveness between the two attachments systems will be determined by calculating incremental cost-effectiveness ratios (ICER), based on baseline–post-intervention differences in satisfaction.

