### Statistical analysis

All quantitative data will be entered and analyzed in a blinded fashion. Such data will undergo descriptive analysis and will be transformed in cases of considerable deviation from normality. Clinical data will generate a composite variable representing clinical adversities; both the compound measure and separate event types will be analyzed.

Mixed linear models will be used to test the effect of interventions and follow-up time (three vs six months), as well their interaction.

The primary outcome will be further tested for carryover effects by fitting another mixed linear model with the two treatment periods and testing for the intervention by period interaction. Other approaches to assess the primary outcome will involve the inclusion of the randomization strata (ridge shape), age, baseline results, and perceived denture base rotation as covariates in separate models, one covariate each time. Analysis for carryover will be performed for cost estimates.

Results will be evaluated according to the intention-to-treat principle. In the case of unbalanced missing data among interventions or loss of 5% (*n* > 1) or more of participants, different strategies will be attempted for imputing primary outcome data, as recommended by Dziura et al. [43]; multiple imputation will be used for patient satisfaction based on least squares regression with at least five datasets. In the case of “missing not at random” (MNAR) data, we will repeat analyses after a baseline-observation-carried-forward approach (i.e. withdrawn participants will be considered as dissatisfied as before receiving implants). A second analysis will be performed with imputed values and cross-checked. Statistical tests will be performed using SPSS 21.0, considering α = 0.05.

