### Risks, participant safety, and trial adherence

Participants may experience the usual postoperative pain and sensitivity associated with minor oral surgical procedures, such as placing dental implants. Specific events may include pain in the surgical site (mandible or mucosa), redness and sensitivity/tenderness of oral mucosa, discomfort associated with changes in prostheses, or discomfort from local anesthesia. These events tend to be transient and localized.

We will record all adverse events observed at each follow-up and at any non-scheduled visits. Possible events include loosening or loss of implants or attachment components, problems with dentures (missing fit, fracture of bases or teeth), and some difficulties to remove and insert the mandibular denture according to a correct pathway. We expect a relatively low rate of occurrence, comparable to other studies [14, 16–18, 20].

Prosthetic adverse effects during the study will be managed as part of the research, by using standard repair or replacement of prosthetic components or dentures, or management of peri-implant tissues. In the unlikely case of a failed implant, we will offer the possibility of replacing it one time at no charge. If the participant does not wish to or cannot receive a replacement, the mandibular prosthesis will be converted to a conventional complete denture by relining or rebasing.

We expect good adherence levels due to the provision of an effective treatment modality (more stable mandibular dentures) as a major benefit combined with the need for regular maintenance recalls, which are integral to overdenture cases. We will also remind participants a few days before each follow-up appointment by telephone or e-mail, according to their preference. Each participant will be offered CAD$ 25.00 per data collection visit as compensation for their travel expenses, corresponding to each three-month follow-up (cross-over stage) and the 12-month final follow-up. A total of CAD$ 75.00 will be offered for the three appointments required for the trial.

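### The six-month cost-effectiveness analysis assumes successful implants and no complications, although the trial foresees, records and repairs such events; followed as written, it leaves their cost out and favours the attachment that needs more repair

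*Protocol article*

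**What the plan says.** The Protocol article, Study outcomes, states the aim of the economic part: "We intend to gather data on both direct and indirect costs to compare the differences in cost-effectiveness between the two attachments systems". The comparison is made by an ICER with general satisfaction as the effect. Three assumptions follow: (1) total six-month cost is the same in both sequences; (2) implant placement is clinically successful at three and six months; and "3) no surgical or prosthetic complications are encountered during the six-month post-treatment period".

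Other sections of the same article treat these events as real:

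- Background gives a reason for testing a new attachment: "Alternatives to well-known attachment systems may result in lower maintenance needs and other favorable characteristics". It also reports that with stud attachments on single implants "more than half of patients may need some reactivation, tightening, or reattachment of retentive components over a single year".
- The list of secondary outcomes at the end of Background includes implant and overdenture success together with complications and maintenance needs.
- Study outcomes has clinician-based outcomes assessed in each three-month period, and Statistical analysis builds a composite of clinical adversities and also analyses separate event types.
- Risks, participant safety, and trial adherence lists loosening or loss of implants or attachment components, poor fit, and fractures of bases or teeth. It expects a relatively low rate and has events recorded at scheduled and unscheduled visits. On handling it says: "Prosthetic adverse effects during the study will be managed as part of the research", by repair or replacement.

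**The concern.** The trial will observe these events and bear their cost, but the one analysis that puts a price on the attachments is built as if they did not happen. The article gives no rule for the ICER when an event does occur. Leaving the participant out would conflict with the intention-to-treat principle in Statistical analysis. Costing the participant as event-free would discard cost data that the trial has collected.

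The direction of the error is predictable. Removing event costs helps the attachment with more events. If Novaloc has the maintenance advantage that Background proposes, the ICER is tilted against it; if it has more problems, the ICER is tilted towards it. The article says under Dissemination and knowledge transfer that economic characteristics will help determine which attachment is more appropriate, so the six-month ICER is meant to be used.

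**Working it through.** **No figure to reproduce.** The article states no six-month event rate and no unit cost. The check therefore asks how likely the zero-event assumption is over a range of rates, and what it removes from the cost difference.

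**Inputs from the article.** N = 26 participants (Sample size estimation). Each attachment is worn for three months, six in total (Study outcomes). Earlier stud attachments are said to need matrix maintenance in more than half of patients per year (Background), taken here as 50%.

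**Assumptions made here.** Annual rates other than 50%, the shape of the hazard, the same rate for both attachments unless stated, and independence between participants.

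**Step 1. Constant hazard.** With annual proportion p, six-month risk = 1 − (1 − p)^(1/2). The chance of no event in 26 participants is ((1 − p)^(1/2))^26 = (1 − p)^13.

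| Annual rate p | Six-month risk | Expected with event, of 26 | Chance of none |
|---|---|---|---|
| 5% | 2.5% | 0.7 | 0.51 |
| 10% | 5.1% | 1.3 | 0.25 |
| 20% | 10.6% | 2.7 | 0.055 |
| 30% | 16.3% | 4.3 | 0.010 |
| 50% | 29.3% | 7.6 | 0.0001 |

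Counting only the three-month Locator period at 50% per year: risk = 1 − 0.5^(1/4) = 15.9%, or 4.1 of 26, and the chance of none is 0.5^6.5 = 0.011.

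**Step 2. Hazard that rises with wear.** Keep 50% at 12 months, but use a Weibull hazard and restart it when the attachment is changed at three months. Survival over both periods is 0.5^(2 × (3/12)^k).

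- k = 2: 0.5^(1/8) = 0.917, risk 8.3%, about 2.2 of 26; chance of none 0.5^(26/8) = 0.105.
- k = 3: 0.5^(1/32) = 0.979, risk 2.1%, about 0.6 of 26; chance of none 0.5^(26/32) = 0.57.

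**Step 3. What is left out of the incremental cost.** Let c be the mean cost for a participant with an event, and r_N and r_L the three-month risks. The omitted part of the Novaloc minus Locator cost per participant is c × (r_N − r_L). At constant hazard, with Locator at 50% per year:

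- Novaloc 0% per year: r_L − r_N = 0.159, or 4.1 participants per 26.
- Novaloc 10% per year: 0.133, or 3.5 per 26.
- Novaloc 25% per year: 0.090, or 2.3 per 26.
- Novaloc 50% per year: 0, so there is no bias.

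The article gives no value for c, so the bias cannot be put in dollars. Only its direction follows: the attachment with the higher risk looks cheaper than it was.

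**The case against.** The defence has several sound parts.

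**The six months may be nearly event-free.** Design calls post-insertion adjustments unlikely. Study outcomes says three months is short for adverse events of other components and puts the appraisal of maintenance at 12 months. Against this, the same section says "A three-month period is enough to observe a significant decrease in the retention force of Locators", and the risks section expects a low rate, not none. The defence limits the size of the problem but does not remove the conflict.

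**Maintenance is not the same as complications.** A reader might infer that the ICER shrinks to component prices and scheduled visits. The article does not say so. Long-term follow-up names maintenance and clinical complications as separate items, so routine matrix care could be costed despite the assumption. The secondary-outcome list joins the two, however, and the risks section counts loose or lost attachment components as adverse events. The boundary is unclear, and that needs settling in the text.

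**The 50% rate.** A reader might conclude that the assumption is almost certain to fail, with a chance of 0.0001. That takes a rate from earlier attachments, applies it to both systems and holds the hazard constant. Step 2 shows it moving to between 0.1 and 0.6 when the hazard rises with wear, so the range is the fair statement.

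**Baseline and sequence totals.** A reader might object that effectiveness is measured as change from baseline. Each participant has one baseline, and (A − baseline) − (B − baseline) = A − B, so it cancels with complete data. A reader might also see a contradiction between assumption (1) and "Analysis for carryover will be performed for cost estimates". Equal sequence totals is the ordinary no-carryover assumption of a two-period cross-over, and planning to check it is proper.

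**Other routes to the answer.** Lower maintenance is one stated rationale beside retention and satisfaction, so it goes too far to say that the trial cannot address its economic question. The 12-month phase also records maintenance, but participants then wear the attachment they chose, so it does not restore the randomised cost comparison.

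**Conclusion.** The point holds for assumptions (2) and (3). The six-month ICER rests on successful implants and no complications, while the same article foresees failures and complications, records and analyses them by period, and repairs them within the trial. Followed as written, the ICER leaves out the cost of observed events and favours the attachment that needs more repair. If the two attachments have equal event costs, or no event occurs, there is no bias.

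The likelihood of at least one event depends on rates that the article does not fix. The chance of none in 26 participants runs from about 0.5 (5% per year, constant hazard) to 0.0001 (50% per year, constant hazard), with about 0.1 to 0.6 at 50% per year under a wear-increasing hazard. The monetary size is unknown. The point concerns a secondary outcome and leaves the primary satisfaction comparison untouched, but it should be corrected before the cost data are analysed.

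**What to change.** In the main six-month ICER, replace assumptions (2) and (3) with the observed costs. Charge all visits, parts, repairs and chair time in each three-month period, whether labelled maintenance or complication, to the attachment in use at the time. Estimate incremental cost and incremental satisfaction as period-adjusted within-participant differences. The period adjustment matters because simple randomisation can leave the sequences unequal: with 16 and 10 participants, (16 − 10)/26 = 23% of any period effect would enter an unadjusted mean difference. Keep the complication-free ICER only as a labelled scenario. Assumption (1) may stay as the no-carryover assumption that Statistical analysis plans to check for costs.

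The cost is more analysis work and wider cost intervals. Event recording and cost collection are already planned. The article states the recording of time and procedures explicitly only for the 12-month phase, so confirm that the cross-over visit form captures them as well.

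### The six-month ICER assumes that no complications occur, so read literally it leaves out repair costs that the trial itself records, while their effect on satisfaction stays in

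*Protocol article*

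**What the plan says.** The Treatment costs item under Study outcomes (protocol article) states the aim: "We intend to gather data on both direct and indirect costs to compare the differences in cost-effectiveness between the two attachments systems". Effectiveness is the change in overall satisfaction, the primary outcome, and the comparison is expressed as an ICER. Three assumptions are listed:

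1. "the total cost at the end of the 6-month evaluation period would be the same between sequences 1 and 2";
2. implants are counted as successes at both the three-month and the six-month assessment;
3. "no surgical or prosthetic complications are encountered during the six-month post-treatment period".

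The article does not relax these assumptions and states no sensitivity analysis around them.

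Other sections bear on the same six months:

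- The secondary outcomes at the end of the Background name clinical complications and maintenance needs together, as one clinician-based outcome.
- Study outcomes has clinician-based outcomes assessed for each three-month period. Statistical analysis builds a composite of clinical adversities from the clinical data.
- Risks, participant safety, and trial adherence lists loosening or loss of implants or attachment components and problems with dentures as possible events, expects them at a low rate, and states that "Prosthetic adverse effects during the study will be managed as part of the research".
- The Background says of earlier stud attachments that "more than half of patients may need some reactivation, tightening, or reattachment of retentive components over a single year", and offers lower maintenance as a possible advantage of newer systems.
- Statistical analysis adds: "Analysis for carryover will be performed for cost estimates".

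**The concern.** The costing rule assumes away events that the trial measures, analyses and repairs in the same window. If it is applied as written, a participant whose attachment component is lost and replaced contributes the satisfaction score that followed, but not the cost of the replacement. The only other literal reading is to leave such participants out of the ICER, which conflicts with the intention-to-treat principle in Statistical analysis. Either way, numerator and denominator no longer describe the same experience.

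Economic variables are a secondary outcome. Both the abstract's Discussion and the Dissemination section look ahead to recommendations that draw on cost. An ICER without event costs cannot inform the part of that recommendation that concerns the cost of complications.

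**Working it through.** The article states no ICER, unit cost or event rate by attachment, so there is no planned figure to reproduce. Two checks are possible.

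**Where the omitted cost sits.** Let C be the mean cost per three-month period and S the mean satisfaction, for Novaloc (N) and Locator (L).

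- ICER = (C_N − C_L) / (S_N − S_L).
- Split cost as C = a + c × e, where a is everything other than events, c is the cost per event and e is the expected number of events per period.
- Assumption (3) sets e_N = e_L = 0, so the numerator loses c × (e_N − e_L). The denominator is observed and does not change.
- The bias is zero only if event costs are equal for the two attachments. If Novaloc has fewer events, the omission makes it look dearer than it is; if it has more, cheaper.

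**How plausible zero events is.** Inputs: 26 participants (Sample size estimation); two three-month periods (Design); a yearly risk of 50%, taken from the Background figure of more than half for earlier stud systems. The time pattern of risk is an assumption, as are the lower yearly risks shown.

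- Constant hazard: cumulative hazard over m months is H = −ln(1 − p_year) × m/12.
- Rising hazard (Weibull, shape 2, 50% at 12 months, restarting when the attachment is changed): each three-month period contributes 0.693 × (3/12)² = 0.0433, a risk of about 4%, against 0.693 × 3/12 = 0.173, a risk of about 16%, under constant hazard.
- Expected participants with an event = 26 × (1 − e^(−H)). P(no event in 26) = e^(−26H).

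| Yearly risk, hazard | Periods at risk | H | Participants with an event | P(no event in 26) |
|---|---|---|---|---|
| 50%, constant | both | 0.347 | 7.6 | 0.0001 |
| 50%, constant | Locator only | 0.173 | 4.1 | 0.011 |
| 50%, rising | both | 0.0866 | 2.2 | 0.105 |
| 50%, rising | Locator only | 0.0433 | 1.1 | 0.32 |
| 20%, constant | both | 0.112 | 2.7 | 0.055 |
| 10%, constant | both | 0.0527 | 1.3 | 0.25 |
| 5%, constant | both | 0.0256 | 0.7 | 0.51 |

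**Illustration of the omitted cost.** Suppose Novaloc halves the 50% hazard and an event costs CAD 50 to 200; both are assumptions.

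- Constant hazard: the difference is 0.173/2 = 0.0866 events per period, so 0.0866 × 50 to 200 = CAD 4 to 17 per participant and period.
- Rising hazard: 0.0433/2 = 0.0217 events, so CAD 1 to 4.

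Without attachment prices in the article, these amounts cannot be set against the rest of the incremental cost.

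**The case against.** The strongest reply is that assumption (3) simplifies a stated expectation. Design calls post-insertion adjustments unlikely. The Risks section expects a low rate. Study outcomes treats 12 months as the period that reveals attachment maintenance for most Locator users. The abstract assigns long-term wear and maintenance to the 12-month phase, where Long-term follow-up records events, time and procedures. Clinical adversities are also analysed separately from the ICER. All of this stands, and it limits the size and importance of the point. It does not justify assigning zero cost to events that do occur.

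Several stronger readings are tempting but not supported:

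- *All maintenance cost is excluded.* Assumption (3) speaks of complications, and Long-term follow-up names maintenance and complications as two things. That attachment maintenance is caught too is a probable inference: the secondary outcomes pair the two, and the Risks section treats component replacement as managing prosthetic adverse effects.
- *The ICER favours the attachment that is cheaper to buy, whatever happens to participants.* It does not. The denominator is observed satisfaction, and direct and indirect costs are both to be gathered, so the incremental cost need not shrink to a price difference.
- *Assumption (3) is almost certain to fail.* The 0.0001 needs a constant hazard at a rate from earlier systems. Retention loss is described as wear-related and the attachment is changed at crossover, so a rising hazard that restarts is at least as reasonable.
- *Assumption (1) empties the cost carryover analysis.* Equal cost by sequence amounts to no cost carryover, and the plan checks for it. Stating an assumption and then testing it is ordinary practice.

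Assumption (2) is also partly defensible. The implant is common to both systems and is placed eight weeks before the attachment, so early implant failure need not be charged to either.

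**Conclusion.** The point holds in a limited form. The stated costing rule conflicts with what the trial records and repairs, and it biases the six-month ICER whenever complication costs differ by attachment. The direction follows from which attachment has more costly events. The size cannot be determined from the article: under the assumptions shown, the chance that assumption (3) holds for all 26 participants runs from about 0.0001 to about 0.5. That chance shows only whether the assumption is safe; the bias itself depends on the cost difference. Severity is moderate: one component of one secondary outcome is affected, the assumptions are openly stated, and the primary analysis and the separate clinical-event analyses are untouched.

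**What to change.** Remove assumptions (2) and (3) from the main ICER. Cost the recorded resource use by attachment and period for all randomized participants: components, chair time, unscheduled visits, repairs and replacements. Give a unit value even to items supplied free of charge. Implant failure before attachment insertion need not be attributed to an attachment. Keep the complication-free case as a labelled scenario, and describe assumption (1) as one that the planned cost carryover analysis will examine. Settle the costing rule before events are seen by attachment.

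If the assumptions are kept, state that the six-month ICER supports no conclusion on complication or maintenance cost.

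The price is some extra costing work and a more variable ICER with a wider interval. Adverse events at scheduled and unscheduled visits and direct and indirect costs are already to be collected. Design, sample size and care are unaffected.
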